## Introduction

 Singapore has been grappling with a persistently low total fertility rate of 1.1 since 2018, which dropped below 1.0 in 2023.^1^ Despite the implementation of comprehensive pronatalist policies, this rate remains among the lowest globally, much like many developed countries in the region.^2 3^ Based on the WHO global report, approximately 1-in-6 couples experience challenges in achieving pregnancy.^4^ Subfertility is defined as the failure to achieve conception after 12 months of regular, unprotected sexual intercourse.^5 6^ Given the high prevalence of poor fertility globally, it is crucial to thoroughly examine the factors that impact reproductive health. Historically, fertility research has been primarily focused on women,^7^ but preliminary estimates suggest that males are solely responsible for 20–30% of cases and contribute to 50% overall.^8^ However, our understanding of the causes, impact and consequences of male reproductive health remains inadequate. Emerging reports indicate that men with impaired fertility bear a higher disease burden, with an increased risk of incident diseases such as heart disease and cancer, as well as premature mortality compared with men with normal fertility.^9^ Following the Paternal Origins of Health and Disease (POHaD) concept, as an extension of the Developmental Origin of Health and Disease paradigm, there is increasing evidence suggesting that the father’s health may significantly affect sperm quality and the health of the offspring.^10^,^12^ Consequently, gaining an understanding of the role of male factors in reproductive health is vital for developing effective interventions to address the fertility crisis, informing strategies for male health promotion and management, and potentially leading to improved health of future offspring.

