#### Cases

Men aged 21–49 years.Men with a female partner aged 21–39 years.Couples who are not able to conceive for at least 12 months of regular, unprotected intercourse.Couples who are Singapore citizens or permanent residents.

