#### Controls

Men aged 21–49 years.Men with a female partner aged 21–39 years.Men with proven fertility indicated by female partners who are currently pregnant and with viable intrauterine pregnancy at gestational weeks of less than or equal to 16 at the time of the study.Couples with attempted time to conceive within 12 months to achieve this pregnancy.Couples who are Singapore citizens or permanent residents.

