#### Cases

Male infertility of a known aetiology, including azoospermia, retrograde ejaculation, genetic disorders, cancer treatment, or testicular trauma.Female infertility diagnosis as confirmed by diagnostic imaging or having severe endometriosis.Female partners with an irregular menstrual cycle of >35 days.Couples with known chromosomal abnormalities.

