We will include the identified male factors from aim 1, along with female factors which are known to be associated with successful pregnancy in a multivariable logistic regression. The male factors will focus on those easily accessible measurements. The female factors include age, BMI, smoking exposure, dietary habit, alcohol consumption and folic acid supplementation, which we have identified in our previous study.^52^ We will also include some important clinical data and other maternal factors such as the duration of active conception attempts, sexual health issues and probable depression in the logistic regression to further select the predictors. To ensure accuracy, we will use weighted logistic regression, adjusting the model based on the updated prevalence of successful pregnancies within a year in the population to correct for sampling biases. The best-fitting model will be determined using Akaike’s information criteria. Subsequently, we will create a point-based scoring system based on the final model coefficients,^53^ making it easily applicable in community settings. Integer points will be assigned depending on the presence or absence of each factor, allowing the estimation of overall probability by summing the points. Higher point values will indicate higher chances of pregnancy. To facilitate calculation of the fertility index score, all continuous variables will be categorised based on clinical thresholds or appropriate percentiles prior to the analysis. We will repeat the same procedures by including male metabolic biomarkers and semen parameters that are associated with successful pregnancy in the weighted logistic regression. This will enable the generation of various versions of the fertility index, catering to different levels of complexity for application in primary and tertiary care settings.

Subsequently, we will use 10-fold cross-validation to assess the performance of the derived logistic regression models and respective fertility index scores. This cross-validation procedure helps evaluate the model’s performance on different subsets of the data, providing an estimate of its predictive ability and generalisation performance. The fertility index will be evaluated for its discriminatory ability in predicting chances of pregnancy based on the area under the receiver operating characteristic curve (AUROC), with value >0.80 indicating that the model exhibits a good discriminatory ability or predictive value.

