### Sample size

There is no straightforward, universally accepted method to estimate the required number of participants for developing a multivariable prediction model. Thus, we employed a few alternative methods to estimate the sample size required. We used paternal BMI as an indicator reflective of paternal lifestyle and metabolic factors that are associated with successful pregnancy and expect that it may be retained in the prediction model. Based on the assumption that males with impaired fertility will have an average BMI 1.3 unit higher than the fertile males,^55 56^ and considering a BMI SD of 4 kg/m^2^, a two-sided 5% type 1 error rate and a power of 90%, the minimum required sample size to detect a difference in BMI between cases and controls is 400 couples (200 cases:200 controls). Considering a variance inflation factor of 1.2 for adjustment of maternal factors and other covariates, the study will need to recruit 480 couples (240 cases:240 controls).

Previous studies have reported the use of the event per variable (EPV) ratio:the number of events (success pregnancy) divided by the number of regression coefficients in the model to determine the sample size of a multivariable model.^57^ An EPV of at least 10 has been recommended to avoid overfitting.^58^ We estimate 15 regression coefficients based on the independent male predicting factors of successful pregnancy in the logistic model. Following this guideline, we require 150 events. Given the observed pregnancy rate of 48% in the population,^59^ the total sample size calculated to achieve this number of events is approximately 313 (150/0.48). By accounting for a variance inflation rate of 1.2 for correlation between male and female factors, we will require 376 couples (188 cases:188 controls) in the study.

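### The Aim 2 weights anchor the fertility index to a population pregnancy rate, but the cases are only non-conceivers without a known cause, so the stated probability is miscalibrated for couples like those sampled

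*Protocol article*

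**What the plan says.** In the protocol article, Statistical analysis plan, Aim 2, the case-control model is to be fitted by weighted logistic regression, "adjusting the model based on the updated prevalence of successful pregnancies within a year in the population to correct for sampling biases". Coefficients become integer points whose sum is meant to give an overall probability of pregnancy. The index is intended for community settings, with versions for primary and tertiary care. Performance is judged by AUROC under 10-fold cross-validation.

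Cases are defined by "Couples who are not able to conceive for at least 12 months of regular, unprotected intercourse" and controls by "Couples with attempted time to conceive within 12 months to achieve this pregnancy".

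The exclusions differ between the groups. Cases lose couples with:
- "Male infertility of a known aetiology, including azoospermia, retrograde ejaculation, genetic disorders, cancer treatment, or testicular trauma"
- "Female infertility diagnosis as confirmed by diagnostic imaging or having severe endometriosis"
- "Female partners with an irregular menstrual cycle of >35 days"
- known chromosomal abnormalities

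Controls lose only pregnancies from donated gametes, known chromosomal abnormalities and known uterine abnormalities.

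The value of the updated prevalence is not given. The only explicit pregnancy rate is in the Sample size section: "Given the observed pregnancy rate of 48% in the population".

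**The concern.** Weighting a case-control sample to a known outcome prevalence recovers absolute probabilities only if each sampled group represents its whole stratum in the population that supplies the prevalence. Here the non-conceiving stratum has been thinned by the case exclusions, while the conceiving stratum is close to unrestricted. The weights then raise the thinned group to the full non-conception rate, so failures due to known causes are counted as if they had occurred in couples without such causes.

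Cycle length shows this most plainly. Couples with cycles over 35 days are barred from the cases but not from the controls, so any such couple in the weighted data is a conceiver.

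What is at stake is the absolute probability, which the index is meant to report and which depends on the intercept set by the anchor. The planned evaluation would not reveal the error. AUROC does not change when the intercept shifts, and cross-validation reuses the same restricted sample.

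**Working it through.** **Inputs from the article.** The anchor is a one-year pregnancy prevalence in the population, with no eligibility limit stated (Aim 2). The 48% in the Sample size section is used there only to convert events into couples. That calculation reproduces: 150/0.48 = 312.5, rounded up to 313, and 313 × 1.2 = 375.6, rounded up to 376. It does not bear on the weighting. I use 0.48 below only as an illustrative anchor.

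**Inputs not in the article.** f is the share of non-conceivers, and g the share of conceivers, with a condition on the case exclusion list. Both are assumed.

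**Formula.** With p the unrestricted one-year rate, the rate among couples without the excluded conditions is

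p′ = p(1−g) / [p(1−g) + (1−p)(1−f)].

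Anchoring to p instead of p′ puts the log-odds too low by logit(p′) − logit(p) = ln[(1−g)/(1−f)]. This gap does not depend on p. It is zero if f = g and positive if f > g, that is, if the excluded conditions lower the chance of conceiving.

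**Results at p = 0.48.** For example, f = 0.50 and g = 0 gives 0.48/(0.48 + 0.52 × 0.50) = 0.48/0.74 = 0.649.

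| f (assumed) | p′, g = 0 | log-odds gap | p′, g = 0.05 | log-odds gap |
|---|---|---|---|---|
| 0.10 | 0.506 | 0.105 | 0.494 | 0.054 |
| 0.20 | 0.536 | 0.223 | 0.523 | 0.172 |
| 0.30 | 0.569 | 0.357 | 0.556 | 0.305 |
| 0.50 | 0.649 | 0.693 | 0.637 | 0.642 |

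With g = 0 the understatement is about 3 to 17 percentage points. A larger g shrinks it: f = 0.50 and g = 0.20 gives 0.384/(0.384 + 0.260) = 0.60, a gap of ln(0.80/0.50) = 0.47. A higher anchor also shrinks it in percentage points: at p = 5/6 with g = 0, f = 0.10 to 0.50 gives 0.847 to 0.909.

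**Simulation check.** In 2,000,000 simulated couples there was one covariate, and 18% had a known cause that lowered the log-odds of conceiving by 2.2. This gave p = 0.504, f = 0.31 and g = 0.05. Cases were drawn only from non-conceivers without a known cause, and the model was weighted to p.

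- Among couples without a known cause the true rate was 0.582, but the weighted model averaged 0.507.
- With the same restriction placed on the controls, it averaged 0.509. The mismatch therefore comes from the anchor, and restricting the controls alone does not remove it.
- Averaged over all couples, the model with unrestricted controls gave 0.507 against a true 0.504.
- The covariate slope was −0.515 with unrestricted controls and −0.502 with restricted controls, against a true −0.5, so associations are little affected.

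**The case against.** The strongest reply is that the index is meant for community use. Several excluded conditions come to light only through a work-up, often after failure to conceive. An uninvestigated couple has no known cause but may have an undiscovered one, and for that couple the population rate may be about right; the simulated community average agrees. This stands, and it limits the claim to couples who truly lack the excluded conditions. It does not rescue the plan, because the index would then assign probabilities to couples with such causes without having sampled any non-conceivers who have them. Cycle length needs no work-up, so the reply does not cover it.

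A second reply is that a condensed article need not define the source of the prevalence. If that source already excludes known causes, the bias shrinks or vanishes. This also stands as a possibility, but the text says only that the rate is the population's and presents the weighting as the correction for sampling bias.

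A reader might infer three stronger points that the article does not support:

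- **That couples who conceive after 12 months fit neither group.** The case criterion admits any couple not yet pregnant after at least 12 months, so such couples are eligible until they conceive.
- **That the article offers two conflicting anchors**, 48% and the Introduction's "approximately 1-in-6 couples experience challenges in achieving pregnancy", which differ by 1.69 in log-odds. Neither is stated as the weighting anchor, and the second is a global figure not described as a one-year rate.
- **That the error is known to be large.** No figure for f or g is given, and taking g = 0 yields the largest gap for any given f.

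**Conclusion.** The weighting rule as written does not match the sample it is applied to. The direction rests on one assumption, that the excluded conditions lower the chance of conceiving (f > g), together with the plain reading that the prevalence is not restricted to eligible couples. Under these, the summed-points probability is too low for couples without the excluded conditions by ln[(1−g)/(1−f)] in log-odds. The size is not determined by the article. In the illustration it runs from almost nothing (0.48 against 0.494 at f = 0.10, g = 0.05) to about 17 points (0.48 against 0.649 at f = 0.50, g = 0). It would be wrong to say that the index is too low for every user. The Aim 1 and Aim 2 associations and the AUROC are little affected; the fault lies in the absolute probability. It should be corrected before the index is derived.

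**What to change.** In the Aim 2 analysis:

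1. Define the index's target population as couples without the conditions on the case exclusion list.
2. Apply those exclusions alike to cases and controls in this analysis, using the medical and reproductive history already collected from both. Note that controls may have been investigated less.
3. Anchor the weights to p(1−g)/[p(1−g) + (1−p)(1−f)], name the source of p, and report a sensitivity range for p, f and g. Clinic screening counts give only an approximate f, because referral may concentrate known causes.
4. If the anchor cannot be supported, report the index as a relative score and drop the statement that it estimates an overall probability.

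Recruitment is unchanged. The cost is a narrower claim, possibly a few controls set aside in this analysis, and a little more analysis work.

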### Statistical analysis plan

#### Aim 1

We will use multivariable logistic regression model to assess the association between case versus control status and male factors, adjusting for potential confounders such as male sociodemographics, general health, as well as female factors which are correlated with both male factors and successful pregnancy. We will identify these potential confounders through a literature review and conceptual framework, guided by directed acyclic graphs. We will explore propensity score methods, such as inverse probability weighting, to ensure balanced distribution of confounders across case and control groups. We will use the least absolute shrinkage and selection operator regression to select male factors for inclusion in the final model.

#### Aim 2

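### Index points come from a refit with no described shrinkage after two selection steps on the same couples, so the probabilities read from them are expected to be too extreme

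*Protocol article*

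**What the plan says.** The Statistical analysis plan describes the route from data to index in order.

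- **Selection (Aim 1).** "We will use the least absolute shrinkage and selection operator regression to select male factors for inclusion in the final model". LASSO has no other stated role.
- **Refit (Aim 2).** "We will include the identified male factors from aim 1, along with female factors" already known to matter. Further clinical and maternal variables are added as candidates.
- **Weighting.** "we will use weighted logistic regression, adjusting the model based on the updated prevalence of successful pregnancies within a year in the population". The stated purpose is to correct for the sampling.
- **Second selection.** "The best-fitting model will be determined using Akaike’s information criteria".
- **Points.** "we will create a point-based scoring system based on the final model coefficients", "allowing the estimation of overall probability by summing the points".
- **Assessment.** "we will use 10-fold cross-validation to assess the performance of the derived logistic regression models and respective fertility index scores". The performance measure named is AUROC, with a threshold of 0.80.

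The Sample size section adds the argument against overfitting: "An EPV of at least 10 has been recommended to avoid overfitting". It counts 15 coefficients, all for male factors.

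**The concern.** LASSO limits overfitting by pulling coefficients towards zero. If it is used only to choose variables, and those variables are then refitted by maximum likelihood, that protection is lost. The refitted coefficients have been selected twice (LASSO, then AIC) and estimated on the same 480 couples, so on average they are too large.

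The remaining steps do not repair this. Prevalence weighting moves the intercept but does not shrink the slopes. Cross-validation follows derivation and is used for assessment, so nothing feeds back into the points. AUROC depends only on ranking, so it is the same whether the linear predictor is right or stretched.

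What is at stake is the probability that a couple is given. High-scoring couples would tend to be told too high a chance and low-scoring couples too low a chance. Several versions of the index are planned for primary and tertiary care, and each repeats the same steps.

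**Working it through.** **1. The plan's own figures reproduce.**
- BMI: n per group = 2(1.960 + 1.282)² × 4² / 1.3² = 199, stated as 200. Then 400 × 1.2 = 480.
- EPV: 15 × 10 = 150 events; 150 / 0.48 = 312.5, stated as 313; 313 × 1.2 = 375.6, stated as 376.

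**2. EPV in the model actually described.** There are 240 couples in each outcome group. On the plan's count, EPV is 240 / 15 = 16. Aim 2 names nine further factors: six female (age, BMI, smoking, diet, alcohol, folic acid) and three others (duration of attempts, sexual health, probable depression). At one coefficient each, 240 / (15 + 9) = 10. With 40 candidates it would be 240 / 40 = 6. Categorised variables with more than two levels would lower it further.

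**3. Expected shrinkage by formula.** The uniform factor S that an unpenalised model needs solves N = P / [(S − 1) ln(1 − R²/S)]. Here N = 480, P is the number of candidate coefficients, and R² is the Cox-Snell value implied by an assumed AUROC at 1:1 sampling (0.121, 0.187 and 0.261 for AUROC 0.70, 0.75 and 0.80). P and AUROC are assumptions.

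| AUROC | P = 15 | P = 24 | P = 40 |
|---|---|---|---|
| 0.70 | 0.81 | 0.73 | 0.62 |
| 0.75 | 0.87 | 0.81 | 0.72 |
| 0.80 | 0.91 | 0.86 | 0.79 |

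Check for P = 24, AUROC 0.80: (0.861 − 1) × ln(1 − 0.261/0.861) = 0.0502, and 24 / 0.0502 = 478, close to 480. The P = 24 column is the EPV 10 case, and S there is 0.73 to 0.86. At AUROC 0.80, reaching S = 0.90 would need 439 couples for P = 15, 702 for P = 24 and 1,170 for P = 40.

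**4. Simulation of the stated chain.** Samples of 240:240 with binary factors; cross-validated LASSO on the male factors; unpenalised weighted refit with nine female factors; backward AIC; integer points. Evaluated in 20,000 new couples, 60 replicates per scenario. Entries for the tenths are predicted / observed.

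| Candidates (male + female) | True AUROC | Prevalence | Mean slope | Lowest tenth | Highest tenth |
|---|---|---|---|---|---|
| 15 + 9 | 0.79 | 50% | 0.825 | 7.6% / 10.6% | 92.4% / 89.1% |
| 30 + 9 | 0.79 | 50% | 0.748 | 6.5% / 11.7% | 93.7% / 88.9% |
| 15 + 9 | 0.71 | 50% | 0.735 | 16.0% / 22.5% | 83.5% / 76.9% |
| 30 + 9 | 0.72 | 50% | 0.663 | 14.8% / 24.0% | 85.0% / 76.3% |
| 30 + 9 | 0.71 | 80% | 0.687 | 42.0% / 55.2% | 95.5% / 92.5% |

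The slope was below 1 in 93% to 100% of replicates. Rounding to integer points changed it by about 0.01 at most. At 50% prevalence the gaps run from 3.0 points (10.6 − 7.6) to 9.2 points (24.0 − 14.8). In the 80% scenario they are 13.2 points at the bottom and 3.0 at the top.

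**5. Does shrinkage help?** A further simulation with AIC and weighting, but no LASSO step, gave median slopes of 0.66 to 0.88, below 1 in 90% to 100% of samples. A cross-validated uniform factor moved the medians to 1.05 to 1.15. It lowered the mean squared error of the probabilities in 68% to 84% of samples.

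**The case against.** **The article does not say that there is no shrinkage.** It is a condensed account, and a fuller analysis plan might penalise the final fit. A reader might infer that the authors have ruled shrinkage out; the text does not support that. What stands is that the article sets out the chain from selection to points step by step, with no shrinkage in it. An analyst following it as written would use the refitted coefficients.

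**The size is conditional.** Signal strength, candidate count and prevalence are not fixed by the documents. A reader might take a stated 90% to be really about 79% and a stated 20% about 30%. Those figures need a slope of 0.6 and an intercept of zero, which is about 50% prevalence. The 48% in the Sample size section would keep the error roughly symmetric, but the article does not say that this is the figure to be used for weighting. At an assumed 80% the top-end gap is small, and most of the error falls at the bottom.

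**The EPV rule is not broken on the plan's own count.** EPV is 16 for the 15 male coefficients, and the recruitment target exceeds the 376 that the rule asks for. A reader might infer that the sample size is in error; it reproduces. What stands is that the count leaves out the female and clinical factors, and that an EPV of 10 would not remove the overfitting.

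**The remedy is noisy.** The estimated factor over-corrects slightly on median and left the slope further from 1 in about 19% to 31% of samples. In a 24-coefficient simulation, the mean absolute error of a couple's probability fell only from 8.5 to 7.6 points at AUROC 0.71, and from 7.8 to 7.5 at 0.80. This is fair: shrinkage corrects the systematic stretch and leaves most of the sampling noise. It is still better on average.

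**The named criterion is untouched.** AUROC does not change under a uniform factor. That is true, but it is also why the criterion cannot detect the problem.

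**Conclusion.** The point holds as an expectation about the method described, not as a certainty for one data set. Followed as written, the plan yields points whose probabilities are on average too extreme.

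The calibration slope is roughly 0.65 to 0.85 for 24 to 39 candidate coefficients and a true AUROC of 0.72 to 0.80. In the mildest case, 15 coefficients and AUROC 0.80, it is about 0.9; that case leaves out the female factors that Aim 2 adds. The error in the extreme tenths is about 3 to 9 points at 50% prevalence. At an assumed 80% it is 1 to 3 points at the top and about 9 to 13 at the bottom. Candidate count, AUROC and the 80% are assumptions.

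The finding concerns the probabilities attached to the points. It does not show that the index ranks couples wrongly. It should be corrected before the index is built, because reporting calibration alone would reveal the stretch but leave it in the published table.

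**What to change.** Add to Aim 2, for each version of the index:

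1. Before assigning points, multiply the final log odds ratios by a uniform shrinkage factor, capped at 1. Estimate it by bootstrap or repeated cross-validation of the whole procedure, with LASSO, AIC and refit redone inside each resample.
2. Re-estimate the intercept under the prevalence weights.
3. Build the points-to-probability table from the shrunken model.
4. Report calibration slope and intercept beside AUROC.

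Keeping penalised coefficients in the final model is an alternative, but it could change the ranking of couples slightly. Under a uniform factor, ranking and AUROC stay the same.

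The cost is a short addition to the analysis plan and more computing, since the resampling has to run within the planned multiple imputation and for every index version. No extra couples or data are needed. The factor is imprecise at this sample size and may over-correct slightly in a given sample, which the authors should acknowledge when they report it.

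### The Aim 2 fertility index categorises every continuous variable before the model is selected and fitted, although classes are needed only when points are assigned

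*Protocol article*

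**What the plan says.** In the Statistical analysis plan, Aim 2, the index is built by a weighted multivariable logistic regression, and AIC determines the best-fitting model. Integer points are then taken from the final model's coefficients and given according to whether each factor is present or absent. To make the score easy to calculate, "all continuous variables will be categorised based on clinical thresholds or appropriate percentiles prior to the analysis". The same procedure is repeated for versions of the index that add male metabolic biomarkers and semen parameters. Neither the cut-points nor the number of classes is stated.

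The Sample size section opens with the difficulty of sizing a multivariable prediction model. It takes paternal BMI as its example and expects that it may be kept in that model. It assumes that "males with impaired fertility will have an average BMI 1.3 unit higher than the fertile males", "considering a BMI SD of 4 kg/m^2", and "a two-sided 5% type 1 error rate and a power of 90"%. From this, "the minimum required sample size to detect a difference in BMI between cases and controls is 400 couples (200 cases:200 controls"). A factor of 1.2 for covariate adjustment brings the total to 480 couples. BMI is treated as a continuous variable throughout this calculation, and nothing is added for categorisation.

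Aim 1 uses logistic regression and LASSO to identify male factors. Nothing in the Aim 1 text says that variables are categorised there.

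**The concern.** The order of steps matters. If the points come from the coefficients of a model fitted to variables already cut into classes, the cut affects selection, estimation and scoring alike. The stated purpose justifies classes only at the last of these, because a fitted continuous function can be turned into points by evaluating it class by class.

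Cutting first treats all men within a class as alike and adjacent men on either side of a cut as different. Two things are at stake in Aim 2. A predictor with a real, graded relation to pregnancy is more likely to be dropped by AIC. Those that stay receive weights estimated less efficiently. The sample size was also argued from the full information in continuous BMI, which this model will not use.

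**Working it through.** **Inputs.** From the Sample size section: difference 1.3 kg/m², SD 4 kg/m², two-sided alpha 0.05, power 90%, 200 per group before inflation, factor 1.2, 240 per group recruited. My assumptions: BMI is normal with equal SD in both groups; cuts are made at percentiles of the pooled 1:1 distribution; after covariate adjustment, 240 per group is worth 240/1.2 = 200. The weighting planned in Aim 2 is ignored.

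**Step 1: the protocol's own figure.** The standardised difference is d = 1.3/4 = 0.325. The normal formula gives n = 2(1.960 + 1.282)²/0.325² = 199 per group; the t-test version gives 200. Then 400 × 1.2 = 480. The stated size reproduces, and power at 200 per group is 90.1%.

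**Step 2: expected test statistic for BMI.**
- Continuous: z = d√(n/2) = 0.325 × √100 = 3.25.
- Median split: 56.5% of cases and 43.5% of controls lie above the cut. z = 0.129/√(2 × 0.5 × 0.5/200) = 0.129/0.050 = 2.58.
- Top-quartile split: 30.1% against 19.9%. z = 0.102/√(2 × 0.25 × 0.75/200) = 0.102/0.0433 = 2.37 (2.365 from unrounded proportions).

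**Step 3: chance that AIC keeps BMI.** AIC keeps a one-coefficient term when its chi-square exceeds 2, that is when |z| exceeds 1.414. The chance is about Φ(z − 1.414).

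**Step 4: power at the 5% level.** This is about Φ(z − 1.960), using the two-proportion formula for the splits.

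| BMI coding | Expected z | Kept by AIC | Power at 5% |
|---|---|---|---|
| Continuous | 3.25 | 97% | 90.1% |
| Median split | 2.58 | 88% | 73.5% |
| Quartile split | 2.37 | 83% | 65.8% |

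The chance of losing BMI under AIC thus rises from about 3% to about 12% or 17%. In terms of the 5% test, a median split would need about 314 per group before inflation, against 200.

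**Step 5: sensitivity to the coding.** Power at the 5% level, effective 200 per group unless stated:
- Tertile cut: 70.4%.
- Cut at the 10th or 90th percentile: 46%.
- Three, four or five nominal classes, omnibus test: 73%, 71%, 68%.
- Three to five ordered classes, trend test: 82% to 86%.
- Full 240 per group, no inflation factor: 74% (quartile) to 81% (median), against 94.5% continuous.

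Every coding checked falls below the continuous analysis on the same footing, but the size of the fall depends on choices that the plan leaves open.

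**Step 6: discrimination by BMI alone.** AUROC is Φ(0.325/√2) = 0.591 continuous, 0.583 in four classes by quartile, 0.565 at a median split and 0.551 at a quartile split.

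**The case against.** The strongest reply concerns what the 90% refers to. A reader might infer that categorisation cuts the study's planned power from 90% to 66–73%. The documents do not support that, for three reasons:

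- The 90% is for a comparison of mean BMI between cases and controls. The categorisation sentence stands under Aim 2, and nothing in Aim 1, where male factors are identified, says that BMI is cut. A continuous comparison there keeps its power.
- Aim 2 selects by AIC, not by a 5% test, so the AIC figures describe the planned procedure better, and they show a smaller loss.
- The plan fixes no cut-points. The range 66–73% belongs to a binary cut between the quartiles at an effective 200 per group; the codings checked at that size run from 46% to 86%. Scoring by presence or absence points towards binary coding but does not settle it.

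These replies stand, and they limit the point to Aim 2 and make its size conditional.

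Three further arguments against categorising are also weaker than they may look. Residual confounding within wide classes is a worry for an association analysis, whereas Aim 2 is prediction. A binary split uses one coefficient, as a linear term does, so extra coefficients are a cost only with more than two classes; splines would use more as well. Finally, a points score still loses some discrimination however the model was fitted. For one monotone predictor with the same classes, its AUROC is the same whether points come from class coefficients or from a fitted curve. The gain from the change is mainly in selection and in the weights.

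None of this justifies cutting the variables before fitting. Points scores are a reasonable format for users, and the format can be kept.

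**Conclusion.** The point holds for the Aim 2 fertility index. As written, the plan discards information before selection and fitting for a reason that applies only to scoring, in the model that the sample size section uses continuous BMI to justify. For that predictor, the chance of retention by AIC falls from about 97% to about 88% (median split) or 83% (quartile split), with power at the 5% level falling from 90% to about 73% or 66%. These figures assume normal BMI, the planned difference and SD, one binary cut, an unweighted analysis and an effective 200 per group. They illustrate one variable and are not a loss for the whole study. The 480 couples are not shown to be too few, and Aim 1 is not shown to be affected. The change is worth making because it is cheap and leaves the score's format as it is.

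**What to change.** In Aim 2, replace the sentence on categorisation with three steps:

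1. Select and fit the models with continuous variables kept continuous: linear by default, or a spline with few degrees of freedom where the budget of 15 coefficients in the Sample size section allows.
2. Form classes only when the score is built. Evaluate the fitted function at a reference value for each clinical class and round to integer points.
3. Report cross-validated AUROC for both the continuous model and the points score, so that the price of the simpler format is visible.

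Apply the same order to the index versions that add biomarkers and semen parameters. The cost is plan wording, a little more programming, and possibly a few extra coefficients if splines are used. No further participants or data are needed, and users still receive an integer score by class.
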